**Fig. 3. fig03:**
[figure not shown]
Structure of the SH+ intervention delivery, supervision and training team.

### SH+ fidelity

Fidelity will be assessed using adherence monitoring checklists to note any deviations from protocol (i.e. a checklist of all activities to be completed in each workshop according to the intervention manual) by both facilitators present at each workshop. Any deviations will be reported to the WHO master trainer after supervision. The clinical supervisor will directly observe a sample of at least 10% of all SH+ workshops, and will complete the same fidelity checklist.

### Ethics and trial procedures

Ethical approval has been obtained from the WHO Ethics Review Committee (ERC), the MildMay Uganda Research Ethics Committee and the Uganda Council for Science and Technology. Permission to conduct research and mental health support activities has been provided by the Office of the Prime Minister in Uganda and the United Nations High Commissioner for Refugees in Uganda.

Potentially eligible women identified through the recruitment process described above will be given oral and written information in the local language about participating in the screening process by a research assistant, who will then seek informed consent for screening. For eligible participants, oral and written information about the trial will be provided by research assistants, and participants will be asked to complete a written consent form. For participants who are illiterate, witnessed oral consent and a thumb print will be considered sufficient. Participants will be free to decline to participate or withdraw without any effect on their routine care.

Small non-financial incentives (e.g. a package of soap) will be provided to compensate participants’ for their time in completing outcome assessments. In case participants do not attend a scheduled assessment, three attempts will be made to contact them to schedule a new appointment, via home visits or contacting other members of the community.

All AEs and SAEs will be recorded by the research team and reported to a data safety monitoring board (DSMB) consisting of an external clinical officer, an external social worker, the project coordinator and the independent assessment team leader. This will occur within 24 h for SAEs and as soon as possible for AEs. A representative from the DSMB will review SAEs within 48 h and, in addition, the DSMB will review all AEs at least twice a month. If necessary, appropriate action will be taken with respect to individual participants, or conduct of the trial (such as referral to specialised care, installing extra assessment points for monitoring participants or discontinuation). No interim analyses are planned. The local project coordinator is responsible for ensuring timely follow-up of any SAEs, and will inform the participants and DSMB if any data indicate that the disadvantages of participation may be significantly greater than expected.

### Blinding and contamination

Participants and implementation staff will not be blind to village allocation. The independent assessment team will remain blind to the intervention allocation of villages throughout the trial, and will operate independently from the intervention team (with offices in separate parts of Arua). All staff have been trained and supervised in the importance of maintaining blinding, and at no time will intentional unblinding of the independent assessment team be required. Prior to conducting each post-intervention and follow-up assessment, instructions will be given by assessors to all participants about the importance of not revealing their village allocation.

Contamination assessments with 15% of participants in each cluster will be conducted at the 3-month follow-up. As these assessments will reveal village allocation, they will be conducted by SH+ facilitators rather than research assistants. Data entry assistants will enter the data into computer systems, and this contamination assessment data will only be entered once all outcome assessments have been completed to prevent unblinding.

Should blinding be compromised for a particular participant, the independent assessment team leader will be alerted. If this occurs during an assessment, the assessment will immediately be halted and a new research assistant will conduct the rest of the assessment. Such assessments will be marked as being conducted by a different research assistant for analysis purposes.

### Statistics

All analyses will be detailed in a statistical analysis plan, which will be signed before unmasking the study data set. As a first step, we will assess the comparability of study conditions at baseline (demographic characteristics, scores on moderators and mediators at baseline) using χ^2^ with continuity correction or Fisher's exact test for frequencies, and independent-sample *t* tests for continuous measures. In the case of any imbalance, we will correct using propensity scoring. We will explore the distributional properties of the outcome variables at all time points and adjust if needed (e.g. using log transformation). Also as a preliminary step, we will analyse crude mean changes on the outcome measures between groups, not corrected for clustering at the village level. This will involve calculating change scores between (T1−T2, T2−T3, T1−T3) scores for the SH+ and EUC groups separately on an intent-to-treat basis (last observation carried forward). These crude change scores will be compared using independent-sample *t* tests, and considered exploratory analyses only.

To test our hypotheses, we will use latent growth curve modelling (LGCM) in a structural equation modelling framework (Duncan & Duncan, 2004). LGCM will be applied to examine statistically significant differences in longitudinal trajectories on outcome measures between the SH+ and EUC groups (over the three time points: T1, T2 and T3). LGCM allows for the modelling of growth processes using participant-specific random intercepts and slopes. The benefit of this approach is that it accounts for clustering as recommended by the CONSORT statement for cRCTs (Campbell *et al*. 2004), builds on data at all time points simultaneously and allows for sophisticated missing data handling.

LGCM will be conducted in three steps. First, we will model growth curves, using all time points [T1 (0 weeks), T2 (7 weeks) and T3 (19 weeks)], and estimate the intervention effect of SH+, compared with EUC alone, on changes over time on the following outcomes: psychological distress (primary outcome), functional impairment, hazardous alcohol use, feelings of anger, interethnic group relations, self-defined psychosocial goals, depression symptoms, PTSD symptoms, psychological flexibility and subjective wellbeing.

Second, we will add potential moderators and their interaction effects to explore variations in intervention effects. Trajectories of outcome measures will be compared between study conditions, while taking into account interaction effects with the following potential moderators of treatment effectiveness: exposure to GBV, trauma exposure to a large range of potentially traumatic events and attendance at sessions. As a secondary analysis, we will test whether baseline levels and types of distress act as moderators. This will be accomplished by creating interaction terms between study condition and moderators of interest. Significant interaction effects will be further probed utilizing model test statements.

Third, a mediation analysis will be conducted to determine whether increases in psychological flexibility with SH+, mediate improvements on: distress, functional impairment, hazardous alcohol use, feelings of anger, interethnic group relations, self-defined psychosocial goals, depression symptoms, PTSD symptoms and subjective wellbeing. In order to assess these mediation effects, we will conduct separate parallel process LGCM analyses (Cheong *et al*. 2003). A parallel process LGCM characterises participant-specific growth processes for a mediator and outcome variable simultaneously, and relates the growth processes with each other while also enabling an assessment of the influence of time-invariant and time-varying variables.

We will use full information maximum likelihood estimation (FIML) as implemented in Mplus 8.15 (Muthén & Muthén, 1998–2017) to adjust the estimates of the parameters to reflect missingness. FIML is considered the appropriate method for handing data missing at random (Schafer & Graham, 2002). Data will be checked prior to the implementation of FIML to address the assumption of missing at random. Results will be presented using point estimates, *p* values, odds ratios (when relevant) and 95% confidence intervals. Difference testing will be conducted to determine if the sample completing the intervention and follow-up assessments is significantly different from those who were lost to follow-up, in basic demographics as well as baseline variables.

Contamination within the EUC village participants (i.e. access to SH+ materials, or other content or messages) will be analysed descriptively. If substantial contamination is identified, contamination-adjusted analyses will be conducted.

In terms of cost-effectiveness, we will apply a societal perspective on costs, including cost of services utilised by participants and losses in productivity. Primary analysis will be on total costs in previous 3 months at T1 and T3. Bootstrap sampling will be repeated 1000 times on skewed cost data. Cost-effectiveness ratios will be calculated by combining total costs with the different effectiveness measures.

Data will be double-entered from paper copies, and data management and descriptive analyses will be conducted in STATA 14.1 (StataCorp, 2015). Analyses testing hypotheses will be conducted using MPlus 8.15 (Muthén & Muthén, 1998–2017) and will be reported according to the CONSORT guidelines for cRCTs.

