### Sample size

Recent meta-analyses of self-help acceptance and mindfulness-based therapies (Cavanagh *et al*. 2014) and psychoeducational depression courses (Cuijpers *et al*. 2009) have found small-to-medium effect sizes for depression symptoms. Although our primary outcome measure is psychological distress, this literature was used as the best estimate of expected effect size. Utilizing the PowerUp! Tool (Dong & Maynard, 2013), a minimum detectable effect size was calculated using an average cluster size of 42 individuals, 14 clusters, intracluster correlation of 0.012, 20% attrition, 80% power, an *α* level of 0.05 and a two-tailed test. With these specifications, the minimum detectable effect size is 0.219 with a total *N* of 588 (294 per condition). In the completed small feasibility cRCT in this population, <20% attrition was observed (Tol *et al*. 2018*a*).

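### Baseline significance tests that ignore village randomisation decide whether propensity-score correction is applied, so chance alone can switch on the adjustment

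*Protocol article*

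**What the plan says.** The protocol article, under Statistics, makes a check of baseline comparability the first step of the analysis. The variables are "demographic characteristics, scores on moderators and mediators at baseline". The tests are chi-squared "with continuity correction or Fisher's exact test for frequencies" and independent-sample t "tests for continuous measures". The next sentence sets the consequence: "In the case of any imbalance, we will correct using propensity scoring". The article gives no threshold for imbalance, no covariate list for the score, and no statement of which analysis the correction enters. The hypothesis tests by latent growth curve modelling are described after this step.

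The same section opens with "All analyses will be detailed in a statistical analysis plan, which will be signed before unmasking the study data set". Under Design, and under Participants, screening and randomisation, the unit of allocation is the village: 14 villages, half to each arm, by simple randomisation after baseline with no balancing constraint stated. The Sample size section gives "an average cluster size of 42 individuals, 14 clusters, intracluster correlation of 0.012, 20% attrition, 80% power".

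**The concern.** Three features of the rule combine badly.

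- **Unit of analysis.** The tests treat women as independent although whole villages are allocated. With any positive intracluster correlation they reject more often than their nominal level. Elsewhere the section credits the growth model with handling clustering and admits that the crude change-score comparisons do not. The balance tests carry neither the correction nor the caveat.
- **What the tests can detect.** Allocation is random by design, so if it was done properly every significant difference is a chance one. Whether a covariate is worth adjusting for depends on how well it predicts the outcome, and a baseline p-value does not measure that.
- **The trigger.** The wording sets no minimum, so one significant variable among several suffices.

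The adjusted or unadjusted form of the analysis is then chosen by the data split by arm. If the correction enters the hypothesis-testing models, which is the natural reading of its place in the sequence, the reported effect depends partly on which chance differences happened to reach significance.

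**Working it through.** The article states no probability for this trigger, so there is no figure of its own to reproduce. Its sample size is internally consistent: 14 × 42 = 588. Only the cluster size and the intracluster correlation are borrowed from that calculation; its minimum detectable effect size plays no part here.

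**Inputs from the article**
- Villages: 14, taken as 7 v 7. Women per village: m = 42. Intracluster correlation: 0.012 (Sample size).
- Variables: five socio-demographic items, A1–A5 (Outcome measures); exposure to gender-based violence and trauma exposure (Statistics, moderators; attendance is not a baseline variable); psychological flexibility (the mediator). That makes k = 8.
- The Statistics section also plans to examine baseline levels and types of distress as moderators. Counting about four such measures gives k = 12.

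**Assumptions, not stated in the article**
- p < 0.05 counts as imbalance.
- Each covariate has intracluster correlation 0.012. The article gives that value only for the sample-size calculation.

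**Step 1: level of one test**
- Design effect = 1 + (m − 1) × ICC = 1 + 41 × 0.012 = 1.492.
- True level = 2 × [1 − Φ(1.96 / √1.492)] = 2 × [1 − Φ(1.605)] = 0.1086, or about 10.9%.

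**Step 2: chance of at least one significant result, independent tests**
- k = 8: 1 − (1 − 0.1086)^8 = 0.60.
- k = 12: 1 − (1 − 0.1086)^12 = 0.75.

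**Step 3: simulation.** This used 7 v 7 villages of 42 women, unadjusted t tests with three continuity-corrected chi-squared tests among them, covariate correlations of 0, 0.3 and 0.5, and 2,500 runs per setting. At ICC 0.012 the per-test rejection rate was 9 to 10%. Ranges below run from correlation 0.5 to correlation 0.

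| ICC of covariates | k = 8, formula | k = 8, simulated | k = 12, formula | k = 12, simulated |
|---|---|---|---|---|
| 0 | 34% | 27–33% | 46% | 31–44% |
| 0.012 | 60% | 45–53% | 75% | 57–74% |
| 0.05 | 91% | 78–87% | 97% | 88–96% |

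Correlation between covariates lowers the chance of at least one hit, so the simulated values mostly lie below the formula. If one demographic item does not vary, k = 7, and at ICC 0.012 the figures are 55% by formula and 41–48% by simulation.

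**Step 4: after the fix.** With covariates fixed in advance, the probability that an observed imbalance changes the model is 0.

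**The case against.** The strongest defence is that the correction is announced in advance and that a statistical analysis plan, not shown here, is to be signed before unmasking. A threshold, a covariate list and the form of the score are details a journal article may fairly leave to that plan. This stands as far as it goes: their absence is not the complaint, and the adjustment cannot be called unplanned. It does not rescue the rule. A plan that kept it, however detailed, would still let comparisons between the arms decide whether to adjust.

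A reader might infer several stronger things that the article does not support.

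- **That the correction would be triggered in most randomisations.** This depends on the number of variables, the threshold and the covariate intracluster correlations, none of which is stated. Near 8 variables at 0.012 it is close to a coin toss. A figure such as 82% needs 15 independent variables, a count with no source in the article.
- **That the primary estimate is certainly affected.** The article does not say that the correction enters the growth model. This is a reasonable inference and no more.
- **That the propensity score would separate the arms.** The listed covariates belong to women and are not village indicators. In simulations of 7 v 7 villages (300 runs per setting), a logistic score on 8 covariates at ICC 0.012 had a mean AUC of 0.58, with fitted scores on average from 0.30 to 0.70. With 15 covariates at ICC 0.05 the AUC was 0.65. No fit failed through separation.
- **That baseline K6 is ignored.** Baseline distress is arguably among the moderators tested, and K6 at T1 is already one of the three outcomes in the growth model.
- **That last observation carried forward biases the primary result.** The crude t tests that use it are disclosed as not corrected for clustering and labelled exploratory. The hypotheses are tested by growth models with full information maximum likelihood.

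**Conclusion.** The concern holds in a limited form. The article fixes a poor rule: woman-level significance tests, in a trial that randomises villages, are the only stated gauge of balance, and a single positive result calls for a propensity-score correction. At the design's own clustering each test runs at about twice its nominal level (9 to 11%). On the assumptions stated above, chance alone would trigger the correction in roughly 45 to 75% of honest randomisations. The lower end is the simulated value for 8 correlated variables and the upper end is the formula for 12 independent ones. Covariate intracluster correlations near 0.05 would take the simulated range to 78–96%. Even without clustering the formula gives 34 to 46%, so cluster-adjusted balance tests would reduce the problem but not remove it. The calculation covers how often the adjustment is switched on; it does not estimate any resulting bias in the treatment effect.

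**What to change.** - Delete the baseline significance tests and the propensity-score rule.
- Present baseline characteristics by arm descriptively.
- Name in the statistical analysis plan, before unmasking, a short fixed set of covariates chosen because they predict outcome (age and trauma count are examples), to be used whatever balance is observed.
- State how the growth model handles baseline K6. It should be used once, through the T1 measurement already modelled as an outcome. Entering it again as a woman-level covariate would not fit a model in which T1 K6 is a response.

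The cost is wording in the analysis plan and, if a village-level covariate is included, one village-level degree of freedom (from 14 − 2 = 12 to 11). No new data are needed, and one analysis step is removed. The Trial status section reports T3 data collection in progress, so the change is available for as long as the data set remains masked.

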## Methods

### Design

This study is a two-arm, single-blind, superiority cRCT, to evaluate the effectiveness of the locally adapted SH+ alongside enhanced usual care (EUC) (SH+), compared with EUC alone. It is conducted in a community-based setting with South Sudanese refugee women living in northern Uganda. All villages in the zones of Rhino Camp where preliminary studies of SH+ have not been implemented (*n* = 14) will be included and randomisation will occur at the village level such that half of the villages will be allocated to receive SH+ and EUC and half will receive EUC alone. Outcomes on a range of mental health indicators will be assessed at the individual level at baseline (T1), post-intervention (T2; 6 weeks) and 3-month follow-up (T3; 19 weeks). The Standard Protocol Items: Recommendations for Interventional Trials (SPIRIT) is outlined in Fig. 1, and the checklist is attached as an online Supplementary file.

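### The growth model is credited with accounting for clustering on the strength of participant-level random effects, which do not cover women within the randomised villages; the village-level term needs to be stated

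*Protocol article*

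**What the plan says.** The Design section fixes the unit of allocation: "randomisation will occur at the village level", and "half of the villages will be allocated to receive SH+ and EUC and half will receive EUC alone". With 14 villages, that is 7 against 7.

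The Sample size section plans for village clustering: "average cluster size of 42 individuals, 14 clusters, intracluster correlation of 0.012, 20% attrition, 80% power", with an alpha "level of 0.05 and a two-tailed test".

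The Statistics section has two layers. The preliminary change-score t tests are described as "not corrected for clustering at the village level" and are exploratory only. The hypotheses are then tested by a latent growth curve model, whose random structure is described in one sentence: "LGCM allows for the modelling of growth processes using participant-specific random intercepts and slopes". The next sentence gives the rationale: "The benefit of this approach is that it accounts for clustering as recommended by the CONSORT statement for cRCTs".

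The rest of that section names full information maximum likelihood as the estimator. It states no village random effect, two-level structure, cluster-robust variance or reference distribution. It defers the detail of all analyses to a statistical analysis plan that is not shown.

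**The concern.** The rationale attributes to the model a property that its stated random effects do not have. A participant's random intercept and slope explain why her T1, T2 and T3 scores resemble each other. They are taken to be independent between women, including women in the same village. In such a model any village variation in change does not disappear. It is absorbed into the between-women slope variance and then averaged over several hundred women instead of over 14 villages. The standard error of the arm difference comes out too small.

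The clustering that matters in a cluster-randomised trial is that of women within villages. An analyst who followed the sentence literally could fit a single-level growth model and believe the village problem solved. The primary K6 comparison and all secondary outcomes use the same model, so all would have intervals that are too narrow and p-values that are too small.

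**Working it through.** **Inputs.** From the Sample size section: 14 villages, 42 women per village, ICC 0.012, 20% attrition, two-sided alpha 0.05. Women analysed per village lie between 42 × 0.8 = 33.6 (completers only) and 42 (all contribute). From the Design section: 7 villages per arm. Assumed: equal village sizes, and an ICC that applies to the analysed contrast, which is change over time.

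**The plan's own figure.** The plan states no type I error beyond the nominal 0.05. Its one computed figure that uses the ICC is the detectable effect: "the minimum detectable effect size is 0.219 with a total *N* of 588 (294 per condition"). The standard two-level formula is M × √[ICC/(0.25 × 14) + (1 − ICC)/(0.25 × 14 × n)].
- With n = 42 the root is √(0.012/3.5 + 0.988/147) = 0.1007. This gives 2.802 × 0.1007 = 0.282 with normal quantiles and 3.051 × 0.1007 = 0.307 with t on 12 df.
- With n = 33.6 the results are 0.305 and 0.332.

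So 0.219 does not follow from the listed inputs alone. An unstated 50% of variance explained by covariates at both levels, with n = 42, no attrition and 11 df, would give 0.2192. That is a separate matter, and nothing below depends on 0.219.

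**Case 1: village omitted.** The design effect is DE = 1 + (m − 1) × ICC, and the true level is 2 × [1 − Φ(1.96/√DE)].

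| ICC for change | m = 33.6: DE, level | m = 42: DE, level |
|---|---|---|
| 0.001 | 1.033, 0.054 | 1.041, 0.055 |
| 0.005 | 1.163, 0.069 | 1.205, 0.074 |
| 0.012 | 1.391, 0.097 | 1.492, 0.109 |
| 0.02 | 1.652, 0.127 | 1.820, 0.146 |
| 0.05 | 2.630, 0.227 | 3.050, 0.262 |

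For the 0.012 row with m = 33.6: DE = 1 + 32.6 × 0.012 = 1.391; 1.96/√1.391 = 1.662; level = 0.097. Only 0.012 comes from the protocol; the other ICCs show sensitivity.

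**Case 2: village modelled, normal reference.** With 7 against 7 villages the contrast rests on 14 − 2 = 12 df.
- Variance corrected for the number of villages, tested against z: 2 × P(t₁₂ > 1.96) = 0.074.
- Uncorrected maximum-likelihood or sandwich variance, too small by 12/14 on average: 2 × P(t₁₂ > 1.96 × √(12/14)) = 2 × P(t₁₂ > 1.815) = 0.095.

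**Case 3: village modelled, small-sample reference.** A corrected variance with the t₁₂ critical value of 2.179 gives 0.05. An uncorrected variance with the same critical value gives 2 × P(t₁₂ > 2.179 × √(12/14)) = 0.067, so the variance correction and the t reference are both needed.

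**Simulation check.** There were 20,000 null trials per setting, 7 against 7 villages, a participant-level change summary and ICC 0.012.

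| Analysis | 34 per village | 42 per village |
|---|---|---|
| Village ignored | 0.099 | 0.107 |
| Uncorrected sandwich, z | 0.097 | 0.093 |
| Corrected variance, z | 0.075 | 0.071 |
| Corrected variance, t₁₂ | 0.050 | 0.049 |

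**The case against.** The strongest reply is that the protocol does mean to correct for village. It labels only the crude t tests as uncorrected for village, says in the next paragraph that the growth model accounts for clustering, plans the sample size with a village ICC, and undertakes to report under the CONSORT guidance for cluster trials. The sentence on participant-specific effects says what the method allows and need not list every term. The variance estimator and degrees of freedom are normally settled in the analysis plan, which is not shown.

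Much of this stands. A reader might infer that village will be left out, or that the type I error is in fact doubled. The document establishes neither. A reader might also treat the missing small-sample reference as a fault in itself. It is not, since an article commonly leaves that to the analysis plan; it matters here only because a corrected specification would be incomplete without it. Nor can one say that planning and analysis use different reference distributions, because the protocol states neither.

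What does not fall is the rationale itself. The protocol chose to say how clustering is handled, and the only random effects it names are at the wrong level. Evidence that a village correction is intended makes the mismatch more important to repair.

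**Conclusion.** The point holds as a misstatement about the primary model, with a conditional consequence. Participant-specific intercepts and slopes do not account for women within villages, and no village-level term is stated.

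- If village were omitted, the true level would be about 0.10 at ICC 0.012 with 33.6 to 42 women per village.
- If village were modelled but tested against a normal reference, it would be about 0.07 to 0.095.
- With a village-level variance and a suitable small-sample reference, it is about 0.05.

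The first figure depends on the ICC for change over time. The protocol does not say that 0.012 is that quantity. The inflation is nearly nil at 0.001 (about 0.054) and large at 0.05 (0.23 to 0.26). All figures assume 7 against 7 villages of equal size. A reader might also conclude that a latent growth model is the wrong primary analysis. The documents do not support that: a two-level version with suitable inference meets the concern.

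**What to change.** 1. Correct the rationale. Say that participant-level effects handle repeated measures and that a village-level component handles the clustering.
2. Specify the primary growth model as two-level, with village random effects on the intercept and on change over time. The effect on change is essential: a village intercept alone cancels out of change and leaves the arm-by-time contrast unprotected.
3. Base the primary p-value and 95% confidence interval on a reference suited to 14 villages, for example t on about 12 df with a variance corrected for the number of villages, or an equivalent small-sample correction. Apply the same rule to the secondary outcomes.

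The growth model can remain primary. The change needs wording and a revised model call, settled before the analysis plan is signed, and no new data. The price is precision. Moving from z to t₁₂ widens intervals by 2.179/1.960 = 1.11. Against a model that ignored village, at ICC 0.012, the factor is √1.391 × 1.11 = 1.31 with 33.6 women per village and √1.492 × 1.11 = 1.36 with 42.
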